### Study limitations

The first limitation that we consider is due to the design of study. Designs that allow participants to choose their treatment are susceptible to confounding factors (including the preference of patients). That is, the characteristics of subjects who choose one treatment may differ from those who choose the other in ways that are related to the outcomes of interest. This weakens the internal validity of the experiment and makes it impossible to isolate the ‘pure’ effect of the respective treatments [31] although this can be controlled with the comparison of characteristics between groups. Related to external validity, almost all eligible patients enter the study, allowing examination of patient characteristics with all the strengths of preferences [32].

As patients’ preferences have a ‘therapeutic effect’ on compliance and motivation, we think they can have a positive effect on patients´ inhalation skills. These effects are similar to the placebo effect [32]. Another related aspect is the Hawthorne effect during the course of the study (that is, the tendency of subjects participating in a research study to change their behavior). Although this could affect overall estimates of the adherence, the implications might be less important in comparing results between the intervention and the control group; furthermore, it is difficult to perceive that any potential Hawthorne effect would be maintained over the many months of this study. Both effects will be taken into account during the analysis.

Another limitation is the selection bias due to missing data. In order to diminish this bias, we will apply several strategies:

An increase of 40 % in the sample size (expected losses)

Three phone calls on different days and times for unreachable patients

Rescue appointments for those who do not attend scheduled visits (three different appointments)

In addition, we take into account the possible contamination between the control and the intervention group because of the relationship between subjects in their daily life (neighborhood, relatives, social networks or associations). However, in another educational intervention study performed with obese patients in our area we did not find a significant level of this effect [33]. We also believe that the intervention characteristics (several steps and individual visits) that we have described will have little influence on contamination between groups.

Another important aspect to consider is the protocol and the intervention standardization. This is why the dynamic has been structured in an exhaustive way and the intervention will be performed by two professionals trained in communication, disease knowledge and inhalation techniques of the different devices used by COPD patients. Furthermore, we have designed a manual for the researchers where we explain the working plan, the different parts of the intervention, the protocol scheme to know what they have to measure each time and the details to assess each variable included in the study. In this way, the procedure can be replicated elsewhere.

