### Outcomes

#### Primary outcome

Performance of correct inhalation techniques. The correct inhalation techniques will be measured by an investigator following SEPAR guidelines [1].

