### Recruitment

Patients will be contacted using their health center records. They will be invited to participate in the study after a brief explanation by telephone about the research aims and they will receive an appointment in the health center. At this first appointment (inclusion visit) patients will receive more detailed information about the study and, if they agree to participate, they will sign the written consent.

At this point, subjects will be asked whether they have a preference for one of the interventions and they will be divided into two groups (Figure 1). Those who select the preference group choose their intervention and they will form two arms of the study. The participants without a preference will join the randomized group and they will be randomly allocated into the three arms of this group.

In the preferences group, the two arms correspond to the two educational interventions designed for this study. In the randomized group the three arms will be: intervention A, intervention B and a control arm.

The randomization will be made using the block randomization technique. The blocks consist of six patients, two subjects per group or three patients, one patient per group (Intervention A, Intervention B and control). The blocks will be marked with a number from 1 to 96 and they will be chosen at random to create the allocation sequence using a sequence of random numbers generated by the Microsoft Excel 2003 program with the function fx:RAND(). The assignment to this group will be made by contacting the person responsible for random sequence by phone. Because the patients are from various health centers, the randomization and the presence of the two interventions and control subjects in all the health centers will be guaranteed.

After randomization all the study data will be recorded and the performance of correct inhalation techniques will be measured in all groups (inclusion visit). In the case of the control group, the inhalation techniques will be tested asking them about how they use their inhalers and the interviewer will write down the mistakes in the template designed. The interviewer will only correct the critical mistakes. In the follow-up visits the subjects will be invited to perform the inhalation technique and the mistakes will be written down.

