#### Control group

Visit one will take place one month after the inclusion visit. Primary and secondary outcomes will be measured (excluding spirometry and quality of life).

Visit two will take place three months after the inclusion visit. All the study data will be recorded.

Visit three will take place six months after the inclusion visit. Primary and secondary outcomes will be measured (excluding spirometry and quality of life).

Visit four will take place 12 months after the inclusion visit. All the study data will be recorded.

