### Statistical analysis

A descriptive statistical analysis will be performed for all the study variables. We will calculate the mean, median and standard deviations for quantitative variables, and the absolute and relative frequency for qualitative variables.

The 95 % confidence interval will be applied. The analysis will be made following an intention-to-treat procedure. The baseline comparison will be made between the main variables that we expected to be related to the primary outcome using the Chi-Square test or an analysis of variance (ANOVA).

The between-group comparison for the primary outcome will be explored using the Chi-Square Test. The Relative Risk Reduction (RRR), the Absolute Risk Reduction (ARR) and the Number Needed to Treat (NNT) will be calculated. Inferences for the secondary outcomes will be made using an ANOVA or Chi-Square test. Each group will be analyzed separately. The comparison using PPS groups is unreliable because of the presence of unknown and uncontrolled confounders. It is necessary to make a comparison between RCT groups alone and analyses which include the PPS groups should be treated as observational studies with known confounding factors adjusted for in the analysis. Then the analysis will be performed following the next steps:

Comparison in RCT group: this will be made between each intervention arm versus control arm (intervA versus control; intervB versus control) and between intervention A and intervention B.

Comparison between RCT and PPS groups: this will be performed between the intervention arms of each group (intervA RCT group versus intervA PPS group; intervB RCT group versus intervB PPS group).

Finally, a logistic regression model will be performed for the primary outcome (performance of correct inhalation technique (yes/no)), considering the intervention as the predictive variable and the rest of the independent measures as the possible modifying factors. We will use the usual 5 % significance level (α = 0.05) and the SPSS statistical package, version 15.0, to run the proposed analysis.

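### The Hawthorne effect is promised a place in the analysis, but no stated analysis uses time, although technique is scored at inclusion and at months 1, 3, 6 and 12 in every arm

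*Protocol article*

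**What the plan says.** Study limitations (Protocol article) gives two arguments about the Hawthorne effect. The first is that "the implications might be less important in comparing results between the intervention and the control group". The second is that "it is difficult to perceive that any potential Hawthorne effect would be maintained over the many months of this study". The paragraph, which also covers the effect of preference, ends: "Both effects will be taken into account during the analysis".

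Technique is scored repeatedly. Recruitment has it measured in all groups at the inclusion visit. The follow-up schedules for control, A and B then repeat it at months 1, 3, 6 and 12, beginning with "Visit one will take place one month after the inclusion visit. Primary and secondary outcomes will be measured".

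The Statistical analysis section lists these inferences:
- Primary outcome: "The between-group comparison for the primary outcome will be explored using the Chi-Square Test".
- Secondary outcomes: "Inferences for the secondary outcomes will be made using an ANOVA or Chi-Square test".
- Contrasts among the randomized arms, and randomized versus preference arms within A and within B.
- One logistic regression of correct technique (yes/no) on intervention, with the independent variables as possible modifiers. The section Independent variables lists patient characteristics, severity, medication and support scores. Visit or time is not among them.

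**The concern.** The second limitation argument is a statement about time, and it is followed by a commitment about the analysis. The preference effect has a matching step; the Hawthorne effect has none. No stated inference includes visit, arm-by-visit, change from inclusion or within-patient correlation.

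What is at stake is the account of the year. A reader will want to know whether the benefit holds, builds or fades. One time-free comparison cannot say. If separate tests at each visit are used instead, differences in significance invite conclusions about fading that the data may not support. Up to four post-inclusion scores per patient would also go uncombined.

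**Working it through.** **1. The plan's own size has no time in it.** Inputs from Sample size: 25 points, 80% power, 95% confidence (taken as two-sided 5%), 40% losses. The control rate is not given there. About 25% correct follows from the up to 75% incorrect in the Discussion.
- 25% versus 50%, pooled formula: 57.7, so 58 per arm; 58/0.60 = 96.7, so 97.
- 37.5% versus 62.5%, unpooled: (1.96 + 0.842)² × (2 × 0.375 × 0.625)/0.25² = 58.9, so 59; 59/0.60 = 98.3, so 99.
- 3 × 99 = 297, 2 × 99 = 198, 5 × 99 = 495, as stated.

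The 99 per arm is therefore a comparison of two proportions at one time point. With 59 evaluable per arm and 25% versus 50%, power is 0.81.

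**2. What a single comparison cannot tell apart.** Assumed courses, each ending at 25% versus 50% at month 12:

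| Course | Arm difference at months 1, 3, 6, 12 (points) | Mean | Month-12 power, 59 per arm |
|---|---|---|---|
| Constant | 25, 25, 25, 25 | 25 | 0.81 |
| Fading | 50, 40, 30, 25 | 36 | 0.81 |
| Building up | 5, 10, 20, 25 | 15 | 0.81 |

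The month-12 test is the same in all three.

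**3. What an arm-by-visit term can and cannot see.** It separates the three rows above. Now add to the constant row an observation effect common to both arms that fades from 20 points to 0. Control is then 45, 40, 30, 25% and intervention 70, 65, 55, 50%, and the difference is still 25 points at every visit. On the percentage-point scale the interaction is zero. The fading shows only in the control arm's own course. That course also contains the correction of critical mistakes which Recruitment allows in controls.

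**4. Combining the visits (illustrative).** Assume 59 per arm at all four visits, a constant effect and an equal correlation ρ between yes/no scores. At one visit, SE = √[(0.25 × 0.75 + 0.50 × 0.50)/59] = 0.086. Averaging four visits multiplies the variance by (1 + 3ρ)/4.

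| ρ | Variance factor | SE of year average | Power, 25 v 50% |
|---|---|---|---|
| 0.3 | 0.475 | 0.059 | 0.99 |
| 0.5 | 0.625 | 0.068 | 0.95 |
| 0.7 | 0.775 | 0.076 | 0.90 |
| 0.9 | 0.925 | 0.083 | 0.84 |

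**5. If the visits were tested separately (the plan does not say so).** With no true effect, four tests at 0.05 and no rule give a chance of at least one false positive of 0.17 at correlation 0.3 and 0.09 at 0.9.

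With a true, constant 25-point effect, the following was simulated: 99 per arm, control 25%, assumed losses of 10, 20, 30 and 40% by months 1, 3, 6 and 12 (only the 40% is in the article), latent within-patient correlation 0.3 to 0.7, 4,000 trials per scenario. Power is about 94% at month 1 and 81% at month 12. Month 1 is significant and month 12 is not in 16 to 18% of trials, although nothing fades.

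**The case against.** **A condensed article leaves models to the analysis plan.** This stands in part. The absence of a GEE is not a finding by itself, and nothing forbids one. What remains is the mismatch inside the article: a commitment about the analysis, and a list of analyses with no step that meets it for the Hawthorne effect as a matter of time.

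**The randomized contrast already takes the effect into account.** This stands. All arms share one visit schedule, so an equal observation effect largely cancels at any one visit, and that is the article's first argument. A reader might infer that the plan depends on fading, or that the Hawthorne effect biases the randomized comparison. The documents support neither: fading is the additional argument, and the section makes the randomized comparison the one to rely on.

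**The remedy does not isolate the effect.** This also stands. Every arm is observed, so no model can separate it, and A and B are re-delivered at each follow-up visit. A change in the arm difference therefore mixes retention with repeated teaching.

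**The harm and the gain are hypothetical.** Largely so. The plan states no visit-by-visit testing, and the discordance figure needs the assumed interim losses. A reader might also infer that the trial throws away a large share of its power. That does not follow: the gain concerns the year average, which is a different quantity from the month-12 difference, it assumes a constant effect, and it is small when the correlation is high (0.84 against 0.81 at 0.9).

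**Conclusion.** The point holds as an inexpensive improvement to the analysis. The article commits to taking the Hawthorne effect into account and appeals to its course over the months, while every stated inference is free of time. The stated tests are valid at one visit, and the 99 per arm is consistent with such a test. They cannot show whether the arm difference is constant, grows or fades, and they do not combine the repeated scores.

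This rests on the wording of the Statistical analysis section and on the visit schedule, not on the simulated figures. The power and discordance figures depend on assumed correlations, a constant effect and, for the discordance figure, assumed interim losses, so they are illustrative.

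**What to change.** **Statistical analysis, randomized group.**
- For correct technique at months 1, 3, 6 and 12, add a GEE with robust standard errors, or a mixed logistic model, with arm, visit, arm-by-visit and technique at inclusion.
- For repeated quantitative outcomes, add a linear mixed model over the visits at which each is measured. Spirometry and quality of life are not measured at months 1 and 6.
- Report the visit-specific arm differences in percentage points beside the year-average difference.
- Base any statement about change in the arm difference on the arm-by-visit test, with its scale named, and not on which visits reach significance.
- Report the control arm's course from inclusion descriptively, noting that it mixes observation with correction of critical mistakes.

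**Study limitations.** Replace the closing promise, as far as it concerns the Hawthorne effect, by a statement that the effect is handled through the randomized contrast and cannot be isolated because every arm is observed.

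**Cost.** Some wording and modest analysis work on data already scheduled; no visit or measurement changes. The year average mixes early and late effects, which is why the visit-specific differences must stand beside it. A changing arm difference still mixes retention with repeated teaching, and the report should say so.

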### Sample size

This was calculated to detect a correct inhalation technique percentage difference between groups of 25 %, with a statistical power of 80 % and a confidence level of 95 %, assuming a percentage of expected losses of 40 %. The final sample size is 495 patients with COPD who meet the selection criteria mentioned above. In the Randomized group it will be necessary to include 297 patients, and in the Preferences group 198 (99 patients per arm).

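### Enlarging the sample for 40% losses is listed as a remedy for missing-data bias, but it protects power only, and the sizing implies a chi-square on observed patients that does not by itself deliver intention-to-treat

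*Protocol article*

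**What the plan says.** Four statements in the protocol article bear on this.

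- **Sample size.** The trial is sized for a "correct inhalation technique percentage difference between groups of 25" percentage points, "with a statistical power of 80"% and "a confidence level of 95"%, "assuming a percentage of expected losses of" 40%. This section and the Discussion give 99 patients in each of five arms, 495 in total.
- **Study limitations.** "Another limitation is the selection bias due to missing data. In order to diminish this bias, we will apply several strategies". Three items follow: an increase of 40% "in the sample size (expected losses"), three phone calls at different times to patients who cannot be reached, and up to three rescue appointments for missed visits.
- **Statistical analysis.** "The analysis will be made following an intention-to-treat procedure". The primary outcome is compared between groups by chi-square at the 5% level. Neither the denominator nor the handling of a missing outcome is described.
- **Follow-up.** Inhalation technique is recorded at inclusion and at 1, 3, 6 and 12 months in every arm.

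**The concern.** Selection bias from missing data arises when the patients who remain differ, in a way related to technique and to arm, from those who leave. Recruiting more patients who then drop out by the same process reproduces the same distortion with a smaller standard error. The article therefore names a real threat and puts first a remedy that cannot act on it. Where bias is present, the extra patients make a spurious difference more likely to reach significance.

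At 40% expected loss on the primary outcome this matters. A reader may take the enlarged sample as protection for the main estimate. The intention-to-treat label may add to that reassurance, but a chi-square test needs an outcome for each patient it counts, so it cannot include lost patients unless a rule supplies their outcomes.

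**Working it through.** **Inputs.** From the article: difference 25 points, power 80%, confidence 95%, losses 40%, 99 per arm. Assumed: a two-sided test, and 25% correct without intervention. The second assumption takes the Background's figure of up to 75% incorrect as the base rate, because the Sample size section gives only the difference.

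**Step 1: reproduce 99 per arm.** Pooled two-proportion formula, 25% v 50%, average 0.375:

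n = [1.96 × √(2 × 0.375 × 0.625) + 0.8416 × √(0.25 × 0.75 + 0.5 × 0.5)]² / 0.25² = 57.7, so 58.

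58/(1 - 0.4) = 96.7, so 97, within 3% of 99. An unpooled calculation at 37.5% v 62.5% gives 59, and 59/0.6 = 98.3, so exactly 99.

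Read literally, a 40% increase gives 58 × 1.4 = 81.2 (82) or 59 × 1.4 = 82.6 (83), not 99. It would cover a loss of only 0.4/1.4 = 28.6%. Covering a 40% loss takes 1/0.6 = 1.67, a 67% increase.

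The match is not unique. A continuity-corrected 70 at 37.5% v 62.5%, times 1.4, gives 98. At the base rate the article reports, however, the 1.4 route gives 82, or 93 with continuity correction, and only division by 0.6 comes close to 99.

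**Step 2: what the sizing implies.** 99 × 0.6 = 59.4 observed per arm. Power for 25% v 50% is:

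| Analysis | Patients per arm | Power |
|---|---|---|
| Observed patients only | 59 | 81% |
| All 99 with outcomes known | 99 | 96% |
| All 99, lost patients counted as incorrect (0.25 × 0.6 = 15% v 0.5 × 0.6 = 30%) | 99 | 72% |

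The planned 80% power corresponds to the first row. The third would need 121 per arm for 80%.

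**Step 3: does enlargement reduce bias?** Assume 40% are truly correct in both arms. One arm loses 50% of incorrect and 25% of correct users, so its loss is 0.6 × 0.5 + 0.4 × 0.25 = 40%. The other arm loses 40% at random. In the first arm, the observed proportion correct is

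0.4 × 0.75 / (0.4 × 0.75 + 0.6 × 0.5) = 0.30/0.60 = 50%, against 40% in the other.

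The sample size does not enter, so the artefact is 10 points at any n. The chance of a significant result is Φ[(0.10 - 1.96 × SE₀)/SE₁] plus a negligible opposite tail. SE₀ = √(0.45 × 0.55 × 2/n) and SE₁ = √[(0.4 × 0.6 + 0.5 × 0.5)/n].

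- Without inflation: 59 enrolled, 59 × 0.6 = 35 evaluable; SE₀ = 0.119, SE₁ = 0.118; about 13%.
- As planned: 99 enrolled, 59 evaluable; SE₀ = 0.092, SE₁ = 0.091; about 19%.

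**Range for the assumed loss pattern** (40% truly correct and 40% lost overall in each arm):

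| Lost in one arm: incorrect / correct users | Observed | 35 evaluable | 59 evaluable |
|---|---|---|---|
| 40% / 40% (random) | 40% v 40% | 5% | 5% |
| 45% / 32.5% | 45% v 40% | 7% | 8% |
| 50% / 25% | 50% v 40% | 13% | 19% |
| 55% / 17.5% | 55% v 40% | 24% | 37% |

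Wherever loss depends on outcome in one arm, the artefact is unchanged by n and the false-positive rate rises with it.

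**The case against.** The strongest reply is that this is a loose sentence in a limitations paragraph of a condensed article. The rule for missing outcomes may sit in a full protocol or analysis plan that is not shown, and its absence here is no error. That stands. It does not cover the sentence itself, which positively states a wrong remedy.

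Four stronger readings are tempting, and the documents do not support them.

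- **That the chi-square is restricted to completers.** No section says so. The stated principle is intention-to-treat, and the observed-case reading is an inference from the sizing.
- **That month 12 is the only endpoint and earlier visits are discarded.** The article fixes no single primary time and does not say that earlier data go unused.
- **That nothing in the plan addresses the bias.** The phone calls and rescue appointments can reduce missingness and hence bias.
- **That the article admits drop-out by allocated arm.** The Discussion's passage on demoralization and drop-out concerns patients with a preference who accept randomization and do not get their choice. Here such patients choose their arm and stay out of randomization. Differential loss remains plausible, since the control arm receives neither intervention, but it is an assumption.

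Nor does the gap between a 40% and a 67% increase make the sample size wrong. The Sample size section speaks of 40% losses, and 99 per arm fits that.

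**Conclusion.** The point holds in a limited form. A larger sample is wrongly presented as a way to diminish selection bias from missing data; it preserves power only. The 99 per arm fits a test on about 59 observed patients per arm (81% power), given the assumed 25% base rate and a two-sided test. The sizing and the intention-to-treat statement therefore need reconciling.

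The size of any bias cannot be known from the documents. The 10-point artefact and the rise in false positives from about 13% to 19% illustrate the mechanism under assumed outcome-dependent loss in one arm; they do not forecast this trial. A reader might compare 59 with 99 evaluable patients, but at 40% loss 99 evaluable would require 99/0.6 = 165 enrolled per arm. The planned inflation moves the evaluable number from about 35 to 59.

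**What to change.** 1. **Reword the first strategy.** Say that the inflation protects power, not validity, and describe it as n/(1-0.4), about a 67% increase. Leave 99 per arm unchanged.
2. **Name the phone calls and rescue appointments as the measures against bias.**
3. **Say how intention-to-treat applies to lost patients in the randomized comparison.** Analyse everyone randomized, as allocated, using the technique data already collected at months 1, 3, 6 and 12. A mixed-effects logistic model (arm, visit, arm by visit, baseline technique) or multiple imputation by arm from the earlier visits would do. Both assume that loss is explained by the data observed.
4. **Add a sensitivity analysis that relaxes that assumption,** such as counting missing as incorrect or a tipping-point shift by arm. The former has about 72% power at 99 per arm, so it suits a sensitivity analysis and not the primary one.

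The cost is some extra analysis work. No further patients, visits or measurements are needed.
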